### 7.2 Adverse event reporting

Adverse events will be recorded on case report forms if they are thought to be associated with GLUMIT-DG study participation in accordance with the adverse event definitions. Adverse events may be discovered during regularly scheduled visits or through unscheduled patient contacts between visits. Summary data on adverse events will be reviewed by the GLUMIT-DG Safety Officer and Executive Committee monthly and will be monitored by the GpCRC DSMB quarterly or more frequently, as needed. These summaries will include analyses comparing rates of adverse events by clinic or in other subgroups requested by the DSMB.

After each meeting of the DSMB, the NIDDK will issue a letter to the investigators regarding the recommendations and advice given to the NIDDK by the DSMB. This will include information about the review of the study data, including adverse events. Investigators will be responsible for transmission of this letter to the IRB at each of the study centers. Analyses or listings of adverse events will not be provided to the IRBs; however, adverse events involving unanticipated problems involving risks to participants, or breaches of protocol which might entail risk to participants will be reported to local IRBs as soon as possible after they are discovered. Each participating center is responsible for ensuring that all local IRB requirements for reporting adverse events are met.

### 7.3 Reporting and adjudication of serious adverse events

All serious adverse events (SAE) must be reported upon discovery at the clinical center per local IRB guidelines. This may involve describing the severity of the adverse event and providing further information. The serious adverse event must be reported in the GLUMIT-DG database together with a memo summarizing the circumstances of the event and the current status of the patient. The NIDDK Program Official will work with the Data Coordinating Center to transmit the serious adverse events to the DSMB Chair and Steering Committee members and all study investigators.

When clinical centers determine that a serious adverse event (see section 7.1 for definition) has occurred, this event must be reported and reviewed by the GpCRC Safety Officer ([name]). Where applicable, signs and symptoms associated with the adverse event will be graded as to severity by the clinical site staff as mild, moderate, or severe using the Common Terminology Criteria for Adverse Events. Examples of SAEs that may occur during the time that a patient is enrolled in the GLUMIT-DG study, that are of particular concern are deaths or severe hypoglycemic or severe hyperglycemic events that may or may not require immediate transport to an emergency department. Any other serious adverse events that occur will be reported and adjudicated.

In addition, an expedited review and adjudication process will be required for “sentinel” adverse events, defined as the subset of severe adverse events involving severe hypoglycemic (<50 mg/dL) or hyperglycemic (>500 mg/dL) occurrences AND any of the following: loss of consciousness, seizures, hospitalization, emergency room visit, professional intervention, or death. While hypoglycemic and hyperglycemic episodes are expected to occur during GLUMIT-DG participation, the frequency of occurrences and the severity of these events will be monitored. More details on the reporting and adjudication of these “sentinel” events are given below.

Adjudication of each sentinel SAE will be done by the standing GLUMIT-DG Serious Adverse Events Adjudication Committee (SAEAC), which has the following membership:

- DCC Safety Officer convenes the GLUMIT-DG SAEAC
- Gastroparesis Clinical Research Consortium Chair and Vice-Chair
- NIDDK Project Scientist
- NIDDK Diabetologist

The SAEAC reviews all pertinent information surrounding the SAE gathered by the DCC from the

clinical center and may request additional information, if needed, to determine the etiology of the event. A decision will be made whether a relationship exists between the SAE and participation in the GLUMIT-DG study, as part of the adjudication of the SAE. The study physicians will be removed from any voting required during the adjudication process if the SAE under review has occurred at one of their respective clinical centers. In the event that an SAEAC member cannot participate within 5 business days, the NIDDK Project Scientist ([name]) will designate a substitute.

The SAEAC will make one of the following recommendations as a result of its adjudication of the SAE: (1) continue the GLUMIT-DG study without interruption, (2) suspend further enrollment (including any patients that may be in the screening process), (3) stop the study, or (4) any other recommendation that the SAEAC deems appropriate. The SAEAC recommendation, with supporting materials, will be communicated to the DSMB, the Steering Committee, and the NIDDK. Recommendations (2) or (3) will require a Steering Committee conference call to consider the process for suspending or stopping the study, with regard to patient safety. The Steering Committee will develop an action plan and rationale for either resuming or stopping the study or responding to any other recommendation that the SAEAC makes. The action plan and rationale must be reviewed by the DSMB and approved by the NIDDK prior to implementation. All clinical centers must also comply with all reporting requirements for their respective IRBs.

The following specific steps outline the process for reporting and adjudication of an SAE in the GLUMIT-DG study:

- 1) Within 72 hours of the time that a clinical center determines that an SAE has occurred, the clinical center must 1) notify the DCC by email and telephone that an SAE has occurred, 2) the clinical center must complete, key, and fax the Interim Event form to the DCC and confirm via email or telephone that the form was received, 3) the clinical center director must complete and send to the DCC a narrative description of the event including the current status of the patient and the planned course for the patient and any other pertinent information, and 4) the DCC must notify the NIDDK Project Scientist and Program Official and provide any sentinel event materials available at the time of the notification
- 2) As soon as possible, but no longer than 10 business days from notification of the SAE, the DCC will convene the SAEAC by teleconference to adjudicate the event as outlined above and to make a recommendation to continue, suspend, or stop the GLUMIT-DG study.
- 3) Within 5 business days, the recommendation and supporting materials will be communicated to the NIDDK, the Steering Committee (i.e., all clinical centers), and to the DSMB.
- 4) If the recommendation is to either suspend or stop the study, within 1 business day, as a precaution, the DCC will notify all clinical centers to immediately suspend further patient enrollment pending the review of and response to the recommendation.
- 5) Within 10 business days, the Steering Committee will develop a written plan of action and rationale in response to the recommendation and submit the plan and rationale to the DSMB and to the NIDDK.
- 6) The DSMB will review the action plan or rationale and provide a recommendation to the NIDDK about the action plan and rationale as soon as possible. At the discretion of the DSMB chair and the NIDDK Program Official, the DSMB review may be either via email and email ballot or via a teleconference.
- 7) Within 10 business days, the NIDDK will communicate its decision regarding any actions that may be required and the DCC and the Steering Committee will move expeditiously to implement these actions.
- 8) Within 1 month (or sooner, if requested) of learning of the sentinel SAE, the clinical center will provide an update on the status of the patient to the DCC and details on the resolution of the SAE.

- 9) The DCC will provide the NIDDK Program Official and the DSMB with a summary all SAEs as part of the quarterly DSMB reports, including an accounting of adherence to the steps outlined above.
-

## 8. Statistical Design and Analysis

---

### 8.1 Hypotheses

#### Primary hypothesis:

- Treatment with an insulin pump will be safe as evidenced by a limited number and extent of (1) mild, (2) moderate, and (3) severe hypoglycemic events as defined previously

#### Secondary hypotheses:

- Treatment with an insulin pump will result in improved glycemic control as evidenced by reductions in hemoglobin A1c levels
- Treatment with an insulin pump will result in improvements in clinical manifestations (efficacy measures) of gastroparesis. These will include symptom benefits as measured by a reduction in Gastroparesis Cardinal Symptom Index (GCSI) and Patient Assessment of Upper Gastrointestinal Disorders Quality of Life (PAGI-QOL) scores as well as gastric and autonomic functional benefits including reductions in gastric slow wave tachyarrhythmias, enhanced tolerance of nutrient consumption on satiety testing, and improvements in cardiac autonomic parameters

### 8.2 Outcome measures

#### Primary outcome measure:

The primary outcome measure for safety is the weekly frequency of mild, moderate, and severe hypoglycemic events identified by discrete glucose measurements (blood glucose values and laboratory reference glucose values when they are available) and as defined in the section above on Safety Monitoring.

The data needed to define the primary outcome measure and other key secondary outcome measures for safety in this pilot study, will be derived from the REAL-Time CGM and insulin pump data, and meter glucose values, which will be recorded and then uploaded for storage and analysis using the web-based system provided by Medtronic (CareLink Personal <http://carelink.minimed.com>). The resulting de-identified data will be retrieved by the Jaeb Center for Health Research for incorporation into an analysis database, which will be transferred to the Data Coordinating Center for derivation of primary and secondary outcome measures and for analysis. The capture and analysis of data will be under the direction of [name] in collaboration with [name] (University of Virginia Health System, Charlottesville, Virginia).

Along with the absolute numbers, the current CareLink software displays the profile of glycemia in a graphic format and calculates the percent time in a 24-hour period that the glycemia is within the range considered hypoglycemia, euglycemia or hyperglycemia. For this study, data will be further analyzed using the analytical methods proposed by Kovatchev and colleagues. The RT-CGMS data is assumed to represent accurately the fluctuations in interstitial glucose that occurs over time and is hence considered in two principal dimensions: risk associated with the amplitude of glucose fluctuations, and time associated with the glucose rates of change. With this understanding, the following parameters will be estimated for secondary analysis: temporal glycemia variability (represented by the interstitial glucose rate of change).

This parameter estimates the slope of the change for blood glucose as a function of time and is calculated for any given time using the following formula:

$[BG(t_i) - BG(t_{i-1})] / (t_i - t_{i-1})$ , where BG = blood glucose and  $t_i$  and  $t_{i-1}$  are consecutive times.

The data will be averaged over time windows of 1 hour and graphically represented by histograms. The

standard deviation of the BG rate of change is a quantitative marker of temporal glycemic variability.

- Low BG Index (LBGI) quantifying the risk associated with both the frequency and the extent of hypoglycemic excursions.
- High BG Index (HBGI) quantifying the risk associated with both the frequency and the extent of hyperglycemic excursions.
- BG risk index = LBGI+HBGI.

These 3 indices are indicators of the risk of hypoglycemia (LBGI) or marked hyperglycemia (HBGI). The overall BG risk index is an indicator of brittleness in glycemia and indicates risk of both hypo- and hyperglycemia. These 3 indices are computed from RT-CGMS data (with no smoothing) and are typically aggregated in 1 hour blocks. The computation is as follows:

Initially, any given blood glucose is transformed by  $f(\text{BG}) = 1.509 \times [(\ln(\text{BG}))^{1.084} - 5.381]$ . The BG risk function is then calculated as  $r(\text{BG}) = 10 \times f(\text{BG})^2$  and separated into left and right branches as follows:

$$\begin{aligned} r_l(\text{BG}) &= r(\text{BG}) \text{ if } f(\text{BG}) < 0 \text{ and } 0 \text{ otherwise} \\ r_h(\text{BG}) &= r(\text{BG}) \text{ if } f(\text{BG}) > 0 \text{ and } 0 \text{ otherwise} \end{aligned}$$

For each hour of observation, the LBGI is the average of  $r_l(\text{BG})$  for a 1-hour period and HBGI is the average of  $r_h(\text{BG})$  for a 1 hour period. Overall LBGI and HBGI are computed as well as the averages for the entire study period.

Plots of LBGI and HBGI (in time) will be visually analyzed to understand the patient's hypoglycemia and hyperglycemia and reveal times of elevated risks and risk trends. Further analysis of the risk estimates will be performed by Poincaré plots. With this graphic representation, a scattered Poincaré plot indicates system instability (glycemia brittleness) and poor glucose control with high risk of BG fluctuations and hence tendency for hypo- or hyperglycemia. The size of the principal axes of a Poincaré plot is used as a numerical marker of system stability.

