### Sample size and statistical analysis of primary outcome

- A total of 40 patients will be enrolled in this pilot study
- Rationale for sample size
  - Primary safety outcome: weekly frequency of mild, moderate, or severe hypoglycemic episodes by discrete glucose meter values and/or a reference blood glucose level if the subject is seen in a hospital (emergency room)
  - Assumed mean weekly mild, moderate, or severe hypoglycemic episodes by discrete glucose values: 0.6
  - Assumed SD for weekly mild, moderate, or severe hypoglycemic episodes by discrete glucose values: 0.8
  - Assumed intra-class correlation between baseline and on-treatment weekly mild, moderate, or severe hypoglycemic episodes by discrete glucose values: 0.6
  - Estimated variance of change from baseline (a minimum of 4 weeks up to 16 weeks) to on-treatment (24 weeks) mean weekly mild, moderate, or severe hypoglycemic episodes (estimated from SD and intraclass correlation, accounting for 3:1 ratio of on-treatment to baseline period lengths): 0.41
  - Type I error: 0.05 (1-sided for equivalence)
  - Power: 0.9
  - Expected percent increase from baseline in mean weekly mild, moderate, or severe hypoglycemic episodes during the treatment period with RT-CGM while using the

- glucose pump: 0%
- Equivalence limit (maximum percent increase in mean weekly mild, moderate, or severe hypoglycemic episodes): 35% (0.6 vs. 0.81 episodes per week)
- Method for sample size calculation: One sample test for equivalence (Chow, Shao and Wang, Sample Size Calculations In Clinical Research, Taylor & Francis, NY, 2003: p. 52-53)
- Software: Centre for Clinical Trials, Chinese University of Hong Kong -- [http://www.cct.cuhk.edu.hk/stat/mean/osm\\_equivalence.htm](http://www.cct.cuhk.edu.hk/stat/mean/osm_equivalence.htm)
- Calculated sample size: N = 37

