**Outcome measures**

- **Primary:** The primary outcome measure is defined as the frequency and extent of mild or moderate hypoglycemic episodes (defined as a capillary glucose level less than 70 mg/dL documented by the home glucose meter and/or a reference blood glucose level if the subject is seen in a hospital (emergency room) setting and absolute number of severe hypoglycemic episodes recorded at the 12 and 24 week follow-up visits while subjects are using a combination of RT-CGM and insulin pump therapy.
- **Secondary outcome measures** will be defined to address the following:  
Effects of RT-CGM and insulin pump therapy on:
  - Hemoglobin A1c at baseline, 12, and 24 week follow-up visits

- 
- Percent time of day in hypoglycemia (<70 mg/dl), euglycemia (70-180 mg/dl), or hyperglycemia (>180 mg/dl) as determined by capillary glucose measurements and in a separate analysis by RT-CGM
  - Glycemia variability (blood glucose rate of change) based on RT-CGM readings
  - Hyperglycemia index and hypoglycemic index using capillary glucose -measurements in one analysis and RT-CGM in a separate analysis
  - Gastroparesis patient-related outcome measures using the GCSI, PAGI-SYM and -PAGI-QOL scores at baseline, 12, and 24 week follow-up visits
  - Maximal volume of water and Ensure consumed during satiety tests at baseline, 12, and 24 week follow-up visits
  - Percent tachygastria, bradygastria and normal 3 cycles per minute (cpm) activity during electrogastrogram (EGG) and satiety testing at baseline, 12, and 24 week follow-up visits
  - Vagal cholinergic and sympathetic adrenergic functions at baseline, 12, and 24 week follow-up visits

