### 2.3 REAL-Time Continuous glucose monitoring system (RT-CGM)

Recently, commercially available continuous glucose monitors have become available to track interstitial glucose levels in real time in patients with diabetes. This method has significant potential to enhance glycemic control in diabetics with frequent hypoglycemic events. Indeed, continuous monitoring detects a

high number of unsuspected hypoglycemic events which are unrecognized by the patient with the traditional finger stick method. Furthermore, this method has been shown to reduce mean hemoglobin A1c values by 0.4% within a 12-week period. From a safety standpoint, continuous glucose monitoring increases the detection rate of nocturnal hypoglycemia in type 1 diabetics.

This study will determine the safety, feasibility, and potential efficacy of using a Real-Time continuous glucose monitoring system (RT-CGM) as an adjunct to capillary glucose measurement to guide insulin pump therapy in patients with type 1 or type 2 diabetes complicated with gastroparesis. Along with the measurement of interstitial glucose concentrations using the RT-CGM, patients in this study will be instructed to perform measurements of blood glucose levels four times daily using a finger stick method with a glucose meter. Throughout GLUMIT-DG Study, patients will be provided with the One Touch® UltraLink or Bayer CONTOUR® Next Link blood glucose meter for self monitoring blood glucose (SMBG) measurements to guide insulin pump therapy. The finger stick blood glucose (SMBG) results will be used for calibration of the RT-CGM and also for glucose monitoring as a guide for insulin therapy. The results from the blood glucose meter will be used to guide insulin infusion with a continuous subcutaneous insulin infusion system (insulin pump).

The RT-CGM system consists of three main components:

- **Glucose sensor:** monitors the interstitial glucose glucose;
- **MiniLink REAL-Time Transmitter:** sends glucose readings from the sensor to the insulin pump; and
- **Insulin pump:** displays and receives glucose readings.

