### 3.2 iPro™ training through the screening period

Patients will initially be instructed by the diabetologist and the diabetes educator on use of the iPro Continuous Glucose Monitor System (CGMS). Patients will then use the iPro CGM or iPro2 CGM for a period lasting at least 2 weeks (or potentially 4 weeks depending on a patient's performance level) to obtain baseline glycemic data. Patients will measure their blood glucose levels 4 times daily using a standard finger stick method (SMBG) with a glucose meter. Depending on availability, patients will be provided with the One Touch® UltraLink or Bayer CONTOUR® Next Link blood glucose meter. Data obtained from the iPro CGM during this training period will not be seen by the patient and will not be used for diabetes management. A successful iPro CGM training period will be defined as the acquisition of continuous recording of glycemic data, in addition to self monitoring of blood glucose (SMBG), for at least 216 hours (9 days) or greater during a 2 week period. If patients cannot successfully master the iPro CGM and collect the required duration of data, they will be offered an additional 2 week period to demonstrate proficiency in the use of iPro CGM to collect the sufficient amount of data (216 hours or more). If the patient is again unsuccessful, he/she will be considered a screen failure and will not be enrolled in the study. Along with showing iPro proficiency, patients must perform 4 blood glucose tests (SMBG) daily, as another indicator of proficiency and compliance in order to continue in the screening phase of the study. Additionally, patients with type 1 diabetes will also be trained on the use of serum ketone meters.

The following additional glycemic data will be calculated from the iPro CGM prior to enrollment in the GLUMIT-DG study:

- Percent time of the day during which prevailing glucose levels are within euglycemic boundaries (80-180 mg/dL).
- Low blood glucose index (LBGI) reflecting the frequency and extent of hypoglycemic episodes.
- High blood glucose index (HBGI) reflecting the frequency and extent of hyperglycemic episodes.
- Glycemia variability standard deviation of blood glucose rate of change.
- Number of episodes of hypoglycemia (glucose <70 mg/dL, mild or severe) per week recorded by the iPro CGM, but not captured by the standard finger stick approach.

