#### 5.4 Run-in visits with insulin pump training

After successful completion of iPro (or iPro2) training, patients will return for four weekly visits, for a minimum of two weeks up to an 8-week learning period to receive training on the usage of an insulin pump coupled with RT-CGM. Participants will be trained on how to use a computer to send the data gathered by the RT-CGM, glucose meter and insulin pump to their study physician and diabetes educator. During the run-in period insulin pump infusion parameters will be adjusted to optimize regulation of blood glucose levels, using information from both their SMBG and from trend analysis of the RT-CGM which will be used only as an adjunct to SMBG.

**Run-in visit 1:** Participants will receive instruction on use of the RT-CGM, including the uploading of the data using the CareLink system as well as instructions on glycemia management using their SMBG which will be supplemented with the trend identification using the RT-CGM. The RT-CGM has a feature known as “REAL-Time Alarms” which will be set to warn patients when their glucose levels are very low or very high. The hypoglycemic alarm threshold will be set at 80 mg/dL and the hyperglycemic alarm threshold will be set at 240 mg/dL. The low glucose snooze will be set between 15-20 minutes to allow time to observe the effect of treatment for the hypoglycemia, and the high glucose snooze will be set to 1-2 hours to allow time to observe the effects of a corrective dose of insulin. They will be taught how to calibrate their RT-CGM using 2-4 glucose readings each day, obtained when there is a low rate of glucose change, as indicated by an absence of rate of change arrows. The subjects will be instructed to not make any insulin dose decisions based on the RT-CGM glucose reading without obtaining a blood glucose measurement using their glucose meter. Insulin doses may be modified based on the glucose rate of change, as was done during the JDRF and STAR 1 and STAR 3 trials. (See package insert for instructions for use of CGM)

**Run-in visit 2:** This visit should be planned within a week after the first run-in visit. Patients will be taught insulin infusion pump mechanics and will be started on an insulin pump filled with saline. The purpose of filling the pump with saline is to ensure that the patient can tolerate wearing it before it is filled with insulin.

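### The primary outcome counts lows found by meter, but RT-CGM alarms from run-in visit 1 change the chance of finding one, so the comparison with baseline mixes detection with risk

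*Protocol*

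**What the plan says.** Section 8.2 defines the primary safety outcome as the "weekly frequency of mild, moderate, and severe hypoglycemic events identified by discrete glucose measurements". The Outcome measures part of the design synopsis words it differently: the frequency and extent of mild or moderate episodes, plus the "absolute number of severe hypoglycemic episodes recorded at the 12 and 24 week follow-up visits". The synopsis sample-size text follows 8.2 and works with a weekly rate: "Assumed mean weekly mild, moderate, or severe hypoglycemic episodes by discrete glucose values: 0.6".

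Section 8.3 tests whether the weekly rate over about 24 weeks on treatment exceeds the rate over a 4 to 16 week baseline by more than 35% (0.6 to 0.81 episodes per week). Section 8.4 gives the DSMB the lower 95% confidence limit of the same percent increase and asks for a vote if it lies above 35%.

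On testing:
- **Screening (3.2, 5.3).** Four finger sticks a day. The patient cannot see the iPro readings, so they cannot prompt a test.
- **From run-in visit 1 (5.4).** "The hypoglycemic alarm threshold will be set at 80 mg/dL and the hyperglycemic alarm threshold will be set at 240 mg/dL". No insulin decision may rest on RT-CGM without a meter reading. At run-in visit 4, patients are taught to take carbohydrate for an RT-CGM warning only once the meter confirms it.
- **At enrollment (5.5).** Patients are taught always to use meter results when treating a low.

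The protocol knows that finger sticks miss lows. Section 2.3 says that continuous monitoring detects a "high number of unsuspected hypoglycemic events which are unrecognized by the patient with the traditional finger stick method", and section 3.2 plans to count baseline lows "per week recorded by the iPro CGM, but not captured by the standard finger stick approach".

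**The concern.** A low enters the primary outcome only if someone puts a drop of blood on a meter while glucose is below 70 mg/dL. In screening, that depends on one of four daily tests falling in the episode. Under RT-CGM, the device under study signals at 80 mg/dL, above the event threshold, and the instructions then call for a meter test. The same number of true lows can therefore yield more counted lows.

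The outcome is not adjusted for the number of tests or for what prompted them. A rise could be better detection, more hypoglycemia or both, and the primary comparison cannot separate them. At stake are the trial's main safety conclusion and the figure put before the DSMB. The protocol itself fixes the measure, the comparator, the limit and the DSMB calculation, so this is not only a matter for an analysis plan.

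**Working it through.** **1. The plan's own figure.** Inputs from the synopsis: variance of change 0.41, one-sided 0.05, power 0.9, limit 0.21 episodes per week (35% of 0.6). One-sample equivalence: n = (1.645 + 1.645)² × variance / limit².
- Limit 0.21: 10.82 × 0.41 / 0.0441 = 100.6, so 101.
- Limit 0.35: 10.82 × 0.41 / 0.1225 = 36.2, so 37.

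The stated N = 37 appears only if 35% is entered as 0.35 episodes per week. That is a separate problem. Below I use the limit as worded (0.21) and show 0.35 beside it.

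**2. Where the switch falls.** Section 5.1 gives screening 2 to 8 weeks and run-in 2 to 8 weeks, which together make the 4 to 16 weeks before enrollment. If all of that is baseline, the run-in share f runs from 2/10 = 0.2 to 8/10 = 0.8. The 3:1 period ratio in the sample-size text implies 24/3 = 8 baseline weeks, but does not say which weeks.

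**3. Apparent rise with no true change.** Let r be the capture under RT-CGM divided by the capture in blinded screening. I assume that capture changes at run-in visit 1 and then stays constant. Then

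apparent rise = r / ((1 − f) + f·r) − 1.

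The values of r are assumptions, since the protocol gives none.

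| Run-in share f | r = 1.35 | r = 2 | r needed for a 35% rise |
|---|---|---|---|
| 0 (screening only) | 35% | 100% | 1.35 |
| 0.2 | 26% | 67% | 1.48 |
| 0.5 | 15% | 33% | 2.08 |
| 0.8 | 5% | 11% | not reachable |

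The last column is 1.35(1 − f)/(1 − 1.35f). It has no solution once f reaches 1/1.35 = 0.74.

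**4. Effect on the primary test.** N = 40, variance held at 0.41, SE = √(0.41/40) = 0.101, upper limit only. Chance of passing = Φ((limit − 0.6 × apparent rise)/SE − 1.645).

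| Apparent rise from detection | Limit 0.21 | Limit 0.35 |
|---|---|---|
| 0% | 0.666 | 0.965 |
| 10% | 0.435 | 0.889 |
| 20% | 0.225 | 0.735 |
| 35% | 0.050 | 0.397 |

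An extra 0.21 per week is one more detected low every 4.8 weeks, or about 5 per patient over 24 weeks.

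**5. Effect on the DSMB calculation.** Taking a one-sided limit and a fixed baseline of 0.6, the observed rise must exceed 35% + 1.645 × SE/0.6.
- N = 40: 35% + 28% = 63%.
- N = 10 (SE 0.202): 35% + 56% = 91%.

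With f = 0.5, an apparent rise of 63% from detection alone needs r = 1.63 × 0.5/(1 − 0.815), about 4.4.

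**The case against.** The best defense has five parts.

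- **Part of the baseline already has alarms.** This stands, and it matters. A reader might infer that testing changes at enrollment and that a 35% gain in capture uses up the whole limit. That holds only if baseline means blinded screening alone. With run-in weeks included, the rise is diluted by an amount that differs between patients, and the baseline also takes in pump treatment started at run-in visit 3.
- **The scheduled minimum is the same, four tests a day.** True, but section 4.4 makes it a floor under RT-CGM, and the alarm acts on when tests are taken as well as how many. Section 5.7 uses readings 1 and 3 hours after meals without saying that these are additional, so I put no weight on them.
- **Retests do not inflate an episode count.** Largely right. Section 6.2 treats retesting as part of one episode and does not limit it to the treatment period. Counts would grow only if readings were counted in place of episodes.
- **The direction is unknown.** Also right. An alarm at 80 mg/dL can avert a low before it reaches 70. Detection bias alone makes passing the limit harder, so it does not by itself give false reassurance. Mixed with prevention, however, the net change cannot be interpreted.
- **Sensor measures are already planned.** The synopsis lists time below 70 mg/dL by meter and by RT-CGM, and section 8.2 adds LBGI. These help, but nothing ties them to the primary conclusion or the DSMB calculation.

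**Conclusion.** The concern holds as a detection asymmetry of unknown size and uncertain net direction. It should be corrected, but it does not invalidate the study. For an assumed 1.35-fold capture gain with no true change, the apparent rise is 35% with a screening-only baseline and 5% to 26% when run-in is 80% to 20% of baseline. Even the middle of that range matters for the test as worded: an apparent rise of 20% cuts the chance of passing from 0.666 to 0.225. These figures rest on the planning variance, a normal approximation and the assumed capture ratios.

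Two stronger conclusions are tempting but unsupported. One is that detection alone is likely to bring the DSMB vote: that needs an observed rise of about 63% at 40 patients, and section 8.4 sets no formal stopping guideline, only a discussion and vote on all available information. The other is that the primary outcome should be cut down to lows from scheduled tests. That would remove documented hypoglycemia from a safety endpoint. Lows treated on alarm could also resolve before the next scheduled test, biasing the count downward, and the protocol sets no clock times by which scheduled tests could be identified.

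**What to change.** 1. Keep all documented meter episodes and all severe episodes in the primary outcome, counting one treat-and-retest cycle as one episode.
2. State in section 8.3 which weeks are baseline, and whether run-in weeks count.
3. Report meter tests per week in each period.
4. Prespecify a supportive comparison of sensor episodes below 70 mg/dL per sensor-week, blinded iPro screening against on-treatment RT-CGM.
5. Prespecify a sensitivity analysis of the meter rate that allows for test frequency. It should remain a sensitivity analysis, because alarm-prompted tests are taken when glucose is low and adjustment can overcorrect.
6. Show items 3 to 5 to the DSMB beside the primary estimate.
7. Use one primary definition in the synopsis and section 8.2.

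The cost is wording and modest extra analysis. Section 8.2 already has RT-CGM and meter data uploaded, and section 3.2 collects the iPro data, so no new visit or device is needed. The sensor comparison has limits: section 3.2 calls the two systems similar, not identical, and a successful iPro period needs only 216 hours, about 1.3 sensor-weeks, so individual baseline rates will be imprecise.
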